#### Statistical power for analyses of leader- and implementation-team data.

We estimated power to test differences in implementation drivers and outcomes of leaders and implementation teams in the HIS and LIS groups. A power analysis was conducted using G*Power [84] and entering a sample size of 78 (39 per group) with four measurement points. Based on repeated measures ANOVA for continuous variables, with alpha set a .05 and assuming a correlation between repeated measurements of .50, the sample of 78 provides excellent power (.95) to detect a small to medium difference (*d* = .33) in differences over time between LIS and HIS groups. We expect little missing data from this collection, but assuming attrition of 20% and a sample size of 62 (N = 31 per group), power still is sufficient (.95) to detect a small-to-medium effect size of *d* = .39.

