### Sample size {14}

Focal populations for each of these assessments include university leaders who support the GlobalConsent implementation (n=5 per university, total of 30); members of implementation teams (n≈5 per University, total≈30 members); fulltime permanent faculty at each university (estimated mean 589 per university, range 186–1038, total 3,532; based on official figures for 2021), and male student participants in GlobalConsent (estimated mean n=796 per university, range 449–1202, total=4,776 18–24 year-old, first-year undergraduate, heterosexual or bisexual men, who are attracted to women; based on official enrolment figures for 2021). We will assume 80% participation and 90% retention in each focal population.

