#### Survey-based data collection (Aim 1 checklist; Aims 2–3).

Survey-based data from all target populations will be collected via REDCap [49], a HIPAA-compliant, web-based data system that allows for the secure collection, transfer, storage, and analysis of study data. Customized surveys will be piloted with individuals like the focal populations but at non-study universities to gauge acceptability, inform final revisions, and assess timings to minimize respondent burden (e.g., 10–15 minutes for each leader, faculty, and implementation team survey; 16 minutes for each student survey). The survey implementation protocol described, above, under “Recruitment” will be followed for at each survey wave for faculty, implementation teams, and students to maximize their participation at baseline (~80%) and retention at endline (~90%), based on prior experience surveying students in Vietnam [51].

Measurement time points will vary for each target sample, according to the project timeline (Figure 2). Leaders will be assessed twice, once before and once after implementation. Implementation teams will be assessed quantitatively at four time points: once before the start of any implementation activities, and once immediately before, during, and after implementation of GlobalConsent. Other data on the implementation will come from administrative records collected by the IT company that is responsible for delivering GlobalConsent. Faculty will complete one assessment before implementation (Year 1) and two after the planned 12-week delivery period of GlobalConsent (Years 3, 5). Three surveys will be administered to students at six-month intervals before the planned 12-week delivery period of GlobalConsent, and three six-monthly surveys will be administered at the same interval after implementation, for a total of six assessments. At each occasion, we will send to students’ smartphones an encrypted link to a REDCap survey with ~189 questions measuring two primary behavioral outcomes and seven cognitive/knowledge, attitudinal/belief, affective, and capacity-related secondary outcomes validated in the efficacy trial [33, 50, 51] (Table 6). Secondary outcomes that are included align with our theory of change (Figure 1) and showed evidence of mediation in the trial [50]. A short modification checklist of 5–10 questions will be administered at the end of each GlobalConsent program module to understand participants’ engagement and satisfaction with the module (Table 4).

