#### Analytical challenges and solutions.

##### Leader and implementation team analysis:

A primary challenge for this analysis is the non-random selection of the sample and relatively small sample sizes across the LIS and HIS groups. These limitations require the analyses to be largely descriptive and inferences to be restricted to the samples rather than to the university populations from which the samples are drawn. Still, our mixed-methods study design will allow us to triangulate findings from the qualitative and quantitative data collected from the university leaders and implementation teams, and both sets of findings with those from university faculty. This multi-method, multi-sample approach will permit a more nuanced understanding of the institutional changes that may be underway and that may facilitate or inhibit the implementation of GlobalConsent and/or planned implementation strategies. Thus, all findings from our approaches to Aims 1 and 2 will inform interpretation of the results for the implementation effectiveness assessment (Aim 3).

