### Dissemination plans {31a}

The final data from this study will include the following from six universities in Vietnam: two rounds of key informant interviews and surveys with 30 university leaders (60 interviews); four rounds of focus group discussions and surveys with six implementation teams (with approximately 8 members each); three rounds of climate surveys with university faculty; and six six-monthly surveys with male university students. We will work with the NIMH Data Archive (NDA) and Emory dataverse to support the preservation, discoverability, and accessibility of data that team members in this project produce. At the project’s completion, we will publish the main findings in peer-reviewed journals. We then will make study documentation, data dictionaries, and the final, cleaned, recoded, and de-identified data available through the NDA and Emory’s dataverse. We will develop a formal data-sharing agreement between collaborators at Emory University, the Center for Creative Initiatives in Health and Population (CCIHP), Georgia State University (GSU) and all participating universities. This plan will describe what data will be shared with participating universities during the project period for analysis and publication and the process for requesting project data. The plan will emphasis equity among participating university and appropriate oversight of data use by key personnel.

Aggregate project findings also may be disseminated widely as working papers on institutional websites, presentations at international and regional scientific meetings, dissemination workshops in Vietnam and the United States, and articles in peer-reviewed journals in the social and behavioral sciences and public health. We will host dissemination seminars at participating universities, at which the study findings will be shared and discussed with university leadership, to guide university policy, campus climate surveys, and campus programming to reduce the incidence of campus sexual violence, with robust attention to the experiences of students. As appropriate, we also will engage regional and national officials in dialogue about the findings, to support evidence-based policies that improve the environment for implementing sexual-violence-prevention programs on university campuses in Vietnam.

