**Potential Drivers of Implementation Outcomes**				
Demographics	Common questions: Age, sex assigned at birth, gender, sexual orientation, ethnicity [33, 61]	8–20^a^	Leaders (Administrator)	1
			General faculty	1
			Implementation teams	1
			Students	1

Institutional norms about sexual violence (SV)^b^	Participation in SV programming	3	Leaders	2
	Perceptions of SV at one’s university	3	General faculty	3
	Perceptions of campus climate [62]	6	Implementation teams	4
	Legal Knowledge of SV [33, 63]	12	Students	3B/3A
	Active consent knowledge [33]	12		
	Rape Myth Acceptance [33, 64, 65]	15		

Implementation leadership^b^	Implementation Leadership Scale [66]	13	Implementation teams	4

Implementation collaboration^b^	Cultural Exchange Inventory [67]	7	Implementation teams	4

Implementation climate^b^	Implementation Climate Scale [68]	12	Implementation teams	4

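### The .95 power for leaders and implementation teams assumes 78 people measured four times, a data set that no outcome in the protocol has

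*Protocol article*

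**What the plan says.** The power section for leader and implementation-team data uses a repeated-measures ANOVA "with alpha set a .05" and "assuming a correlation between repeated measurements of .50", "entering a sample size of 78 (39 per group) with four measurement points". It describes the resulting .95 at d = .33 as excellent. It adds a variant with 20% attrition (62 people, d = .39, again .95). The analysis section for leaders and implementation teams also works with about 78 people.

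Other sections describe different data:

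- **Survey waves.** The survey-based data collection section states: "Leaders will be assessed twice, once before and once after implementation". Implementation teams are surveyed four times. Table 5 agrees on both.
- **Team size.** The sample-size section has 30 leaders and "members of implementation teams (n≈5 per University, total≈30 members". The Aim 1 outcomes section describes focus groups of 5 to 8 team members per university. The dissemination section refers to "six implementation teams (with approximately 8 members each".
- **Who answers what.** In Table 5 the leadership, collaboration and climate scales (the first is the "Implementation Leadership Scale [66"]) are listed for implementation teams only. Institutional norms and the six acceptability, appropriateness and feasibility scales are listed for leaders and teams alike.
- **Status of the analysis.** The section on analytical challenges says of this analysis: "These limitations require the analyses to be largely descriptive and inferences to be restricted to the samples".

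**The concern.** A repeated-measures calculation takes its information from the number of people multiplied by the number of waves. Entering 78 × 4 credits the 30 leaders with two surveys they will not complete. It also assumes eight members per team where the sample-size section plans about five. For the three team-only drivers, which the analysis section names as its examples of drivers, it counts 30 people who supply no data at all.

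What is at stake is how these Aim 2 comparisons are read. The analysis section plans tests at p < .05 and a Group × Time interaction, and the protocol tells the reader that the interaction has high power. A reader who relies on that statement would give a non-significant result on, say, implementation climate more weight than the design supports.

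**Working it through.** **1. Where 78 comes from.** The protocol does not derive it. Leaders: 5 × 6 = 30. Teams at 8 each: 6 × 8 = 48, and 30 + 48 = 78. Teams at 5 each: 6 × 5 = 30, and 30 + 30 = 60. So 78 requires the team size in the dissemination section, not the one in the sample-size section.

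**2. Reproducing the stated figure.** Within-between interaction, two groups, m waves, correlation ρ = .50, α = .05, sphericity, f = d/2:

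λ = f²·N·m/(1 − ρ), df1 = m − 1, df2 = (N − 2)(m − 1), with power from the noncentral F distribution.

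- N = 78, m = 4, d = .33: λ = .165² × 78 × 4/.5 = 16.99, df 3 and 228, power .944.
- N = 62, m = 4, d = .39: λ = .195² × 62 × 4/.5 = 18.86, df 3 and 180, power .963.

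Both agree with .95 to within two percentage points.

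**3. One group at a time, same formula, d = .33.**

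| Data | λ | df | Power | d for .95 power |
|---|---|---|---|---|
| Team-only drivers, 48 × 4 | 10.45 | 3, 138 | .77 | .43 |
| Team-only drivers, 30 × 4 | 6.53 | 3, 84 | .54 | .55 |
| Leaders alone, 30 × 2 | 3.27 | 1, 28 | .42 | .68 |

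**4. Shared measures, leaders and teams pooled.** A mixed model accepts unequal numbers of waves. I used generalised least squares with constant correlation .50 and placed leaders at the first and last team waves. The group difference over time was scaled to f = .165 over four waves, and df2 was approximated as 3(n teams − 2) + (n leaders − 2). The effect shapes were a linear drift and a step at the second, third or fourth wave. As a check, 78 people at all four waves again give λ = 16.99 and power .944.

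| Data | λ over shapes | df2 | Power |
|---|---|---|---|
| 48 team members × 4 + 30 leaders × 2 | 13.7 to 16.3 | 166 | .88 to .93 |
| 30 team members × 4 + 30 leaders × 2 | 9.8 to 12.4 | 112 | .74 to .84 |

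Simple bounds for the second row are .71 (60 × 2) and .86 (60 × 4).

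**5. The attrition variant.** At d = .39 and with no attrition, power is .90 (teams, 48 × 4), .70 (teams, 30 × 4) and .54 (leaders, 30 × 2). The variant therefore does not cover these cases.

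**6. A different test.** The between-groups test, λ = f²·N·m/[1 + (m − 1)ρ] with f = .33, also gives about .95 for 78 × 4 (.953), and .969 for 62 × 4 with f = .39. Under it, teams have .81 (48) or .60 (30) and leaders alone .52. These values are higher, but the direction is the same.

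**The case against.** The strongest reply is that the power section concerns leaders and teams together, and the planned Group × Time model can use everyone's available waves. Most survey measures in Table 5 are shared. With eight per team, the missing leader waves then cost only about 1 to 6 points (.944 against .88 to .93). This stands. It means that .77, .54 and .42 must not be read as the power of the whole Aim 2 analysis. They belong to team-only drivers and to leaders analysed alone. The wording that separates targets is attached to the mean comparisons within each period, not to the interaction test.

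Second, the documents do not establish that five per team is right and eight is wrong. That also stands: .54 and .74 to .84 are the lower cases, not corrected values.

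Third, the protocol admits small samples, limits inference to the samples and plans triangulation with qualitative and faculty data. Leaders and team members are chosen purposively, so no recruitment target depends on this figure. This lowers the consequence. A reader might infer that null results are bound to be misread as no difference, but the stated limitation argues against that. It does not correct the power statement, and the two passages still pull in different directions.

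A reader might also infer that the .95 is a calculation error, or that p < .05 tests must be dropped. Neither follows. The arithmetic reproduces, and a largely descriptive analysis can still contain tests.

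**Conclusion.** The point holds as a conflict of inputs. The claimed .95 describes 78 people with four measurements each, and no outcome in the protocol will have that. At d = .33, power on the protocol's own numbers is:

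- about .88 to .93 or .74 to .84 for pooled shared measures, depending on team size;
- .77 or .54 for the three team-only drivers;
- .42 for leaders alone.

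These figures rest on the protocol's ρ = .50 and α = .05, the interaction test with d = 2f, full retention, sphericity and no clustering. The pooled ranges also depend on the assumed effect shapes and on leaders' surveys lining up with the first and last team waves.

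The planned model nests people within six universities, while the stated ANOVA inputs include no university term. A reader might infer a particular further loss from this. The protocol gives no intraclass correlation or university-by-time variance, so no size can be put on it.

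Confidence is high on the inconsistency and moderate on the exact power values. The student and faculty power statements are not affected.

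**What to change.** 1. State one implementation-team size, or one range, and use it in the Aim 1 outcomes, sample-size, leader and team analysis, leader and team power, and dissemination sections.
2. Replace the single .95 statement and its 20% attrition variant with separate power values or detectable differences for (a) measures shared by leaders and teams and pooled with their actual waves, (b) team-only drivers with four waves, and (c) leaders with two waves. Name the test and the definition of d.
3. Say that these figures ignore clustering in six universities, or show them over an assumed range.
4. Bring the description of the power as excellent into line with the limitation stated under analytical challenges.

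This costs a short recalculation and some rewording. No change to design or data collection is needed. The stated power will be less favourable.

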#### Analysis of quantitative data from leaders and implementation teams (Aim 2).

One set of analyses to explore primary hypotheses for Aim 2 will examine changes over time across LIS and HIS groups in implementation drivers and outcomes among university leaders and implementation teams (Table 5). Quantitative analyses will focus on the same measures across implementation groups for comparisons within and across periods. Cronbach’s α will be estimated with the total sample (N≈78) using pre-implementation baseline survey data to confirm the internal consistency of each scale. Quantitative responses within item sets will be summed, and scores will be standardized by averaging the items in each scale. We will examine correlations of scale constructs at each time point. Comparisons between HIS and LIS groups will be conducted within each time period by target (i.e., faculty, leaders, implementation teams) to examine whether mean differences are statistically significant, at p<.05. We also will examine HIS and LIS group differences in means for implementation drivers (e.g., perceptions of leadership, collaboration, climate) and implementation outcomes (e.g., intervention acceptability, appropriateness, feasibility) at each time point. We will test for differential change over time in mixed models by testing Group x Time interactions with target responses nested within participating university.

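### The power of .95 stated for leaders and implementation teams does not hold for a difference in change of d = .33; with the protocol's own inputs it is about .2 to .4, and at most .53

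*Protocol article*

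**What the plan says.** The Aim 2 analysis section for leaders and implementation teams names the test: "We will test for differential change over time in mixed models by testing Group x Time interactions with target responses nested within participating university". The power paragraph that follows reports a G*Power calculation for a repeated-measures ANOVA, at a 5% significance level and with correlation .50 among the waves. The size of the sample is described as "entering a sample size of 78 (39 per group) with four measurement points". The conclusion is that "the sample of 78 provides excellent power (.95) to detect a small to medium difference", where the effect is given as d = .33 and described as a difference between the groups in their differences over time. For 20% attrition, leaving 62 people, the paragraph repeats the .95, now at d = .39 ("power still is sufficient (.95) to detect a small-to-medium effect size of" that value). It gives no value of f, no G*Power routine and no pattern over the four waves.

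**The concern.** G*Power's repeated-measures ANOVA routines take Cohen's f, whereas the protocol reports d. For two groups at one time point, d = 2f. For a Group x Time interaction, f is the spread of the interaction effects over all eight group-by-wave cells, so a given difference in change corresponds to a much smaller f than d/2. A power of .95 for a .33 SD difference in change with 39 people per group therefore looks too high.

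What is at stake is the interpretation of this part of Aim 2. A reader who trusts the .95 would expect a small-to-medium differential change to be found almost every time. If the power is really below one half, a non-significant interaction says little about whether the higher-intensity bundle shifts these measures.

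**Working it through.** **Inputs (power paragraph).** N = 78 (39 per group), m = 4 waves, r = .50, alpha = .05, d = .33. Second scenario: N = 62, d = .39. Outcome SD is set to 1.

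**Formulas (G*Power, noncentral F).**
- Between-groups main effect: λ = f²·N·m / (1 + (m−1)r), df 1 and N−2.
- Within-between interaction: λ = f²·N·m / (1−r), df m−1 and (m−1)(N−2).

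**Step 1: reproduce the .95.** Four ways of turning .33 into f, at N = 78:

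| Routine | f | λ | Power |
|---|---|---|---|
| Between groups | .33 (f = d) | .33²·312/2.5 = 13.59 | .953 |
| Interaction | .165 (f = d/2) | .165²·312/.5 = 16.99 | .944 |
| Between groups | .165 (f = d/2) | 3.40 | .444 |
| Interaction | .33 (f = d) | 67.95 | 1.000 |

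Only the first two come close to .95. The first reports f as d and tests the average group difference, not Group x Time. The second applies a two-group conversion to an interaction. For N = 62 and .39 the same two settings give .969 and .963. Solving for exactly .95 at N = 62 gives f = .368 (between groups) or 2f = .376 (interaction), so the printed .39 is matched only approximately.

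**Step 2: f for a difference in change.** Let g_t be the gap between groups at wave t. The interaction effects in the cells are ±(g_t − mean g)/2, so f = SD(g_t)/2, with the SD taken over the four waves. If the gap moves between 0 and d, SD(g_t) is at most d/2, so f is at most d/4.

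| Gap over four waves | f | f at d = .33 |
|---|---|---|
| Linear: 0, d/3, 2d/3, d | .186d | .0615 |
| Step after wave 1: 0, d, d, d | .2165d | .0714 |
| Step after wave 2: 0, 0, d, d | .25d | .0825 |

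**Step 3: power with that f.** For the step after wave 2 at N = 78, λ = .0825²·312/.5 = 4.25. On 3 and 228 df this gives .373. A 1-df contrast that matches the true pattern exactly has the same λ on 1 and 76 df, giving .530.

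| Pattern | N = 78, d = .33: 3 df | matched 1 df | N = 62, d = .39: 3 df | matched 1 df |
|---|---|---|---|---|
| Linear | .218 | .329 | .238 | .357 |
| Step after wave 1 | .286 | .422 | .313 | .456 |
| Step after wave 2 | .373 | .530 | .409 | .570 |

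As a check, a simple two-wave comparison of change with N = 78 and d = .33 gives .30 (with r = .50 the SD of change equals the raw SD).

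**Step 4: detectable difference in change at .95 power, 3-df test.** The interaction needs f = .167 at N = 78 and f = .188 at N = 62. Dividing by the factors in step 2:
- N = 78: .67 SD (step after wave 2), .77 SD (step after wave 1), .90 SD (linear).
- N = 62: .75, .87 and 1.01 SD respectively.

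**The case against.** **The cause is not documented.** A reader might infer that the f-for-d confusion is established. It is not: the article gives neither routine nor f, two different explanations fit, and neither reproduces the N = 62 line exactly. The low power in step 3 does not depend on which explanation is right.

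**The d may be only a label for 2f.** On that reading, f = .167 lies between Cohen's conventional small (.10) and medium (.25) values of f, and .95 is a correct interaction power. But the text describes the effect as a between-group difference in change over time, and an f of .167 requires that difference to reach .67 to .90 SD. Likewise, if the gap grew by .33 SD at every wave, power would be .98. That is a total divergence of .99 SD, which does not fit the article's description either.

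**The consequence is already limited.** The section on analytical challenges says that this analysis must be largely descriptive, with inference restricted to the sample and triangulated with other data. This stands. One might infer that a null result would be reported as evidence that the higher-intensity bundle does not work; the document does not support that, and no student-level effectiveness outcome rests on this paragraph. The caveat does not correct the printed figure, however, and tests at p<.05 are still planned.

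**A focused contrast would rescue power.** Not in general. The matched 1-df figures assume that the true pattern is known beforehand. A fixed contrast of the last two against the first two waves gives .53 under a step after wave 2 but only .17 under a step after wave 1, below the .29 of the 3-df test.

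**Conclusion.** The point holds as an error in a stated figure. With the protocol's own inputs, a .33 SD difference in change has power of about .22 to .37 on the Group x Time test, against the stated .95. The most favourable matched contrast reaches .53, still 42 points short. The attrition line is wrong in the same way: .24 to .41, at most .57.

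The result assumes that d is in outcome-SD units and that the gap moves from 0 to d over the four waves. Under that assumption .53 is a ceiling, but .22 is not a floor, because a poorly matched contrast gives less. The calculation also takes 78 people at four waves as given and ignores nesting within six universities. The article's other sections are less favourable: Sample size {14} gives 30 leaders and about 30 team members, the data-collection section has leaders surveyed only twice, and 78 is reached only with the teams of about eight in the dissemination section (30 + 6 × 8). With 60 people and four waves for all, power at .33 SD is .17 to .29 on the 3-df test, and .43 at best.

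**What to change.** Keep the sample and the planned analysis, and correct the power paragraph:

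- Name the G*Power routine and the f entered, and define the effect as a between-group difference in change in SD units with its assumed pattern over waves.
- Under the stated inputs, give the detectable difference at .95 power as about .67 to .90 SD for 78 people and .75 to 1.01 SD for 62. Alternatively, give power at .33 SD as about .2 to .4 for the omnibus test.
- Remove the descriptions of the power as excellent and of the detectable effect as small to medium, in both scenarios.
- Base the final figure on the people and waves actually planned, after reconciling Sample size {14}, the survey schedule and the dissemination section. Table 5 measures leadership, collaboration and climate in implementation teams only, so no total that includes leaders applies to those scales. State that the figure ignores nesting within six universities.

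The cost is a short recalculation, new wording and a less favourable detectable effect. No further participants or data are needed.
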